**Statistical analysis**

Endpoints will be evaluated as differences between treatment groups. Categorical data are analyzed by chi2 or Fisher’s exact test. Depending on normal distribution, continuous data is analyzed by either un-paired Student’s *t-test* or Mann-Whitney rank sum test. An Intention-to-treat principle will be used including all randomized participants in the analysis. Stratification will be performed, and confounding factors (sex, age, surgical indication, BMI, smoking, comorbidity) analyzed in a multiple logistic regression model. Repeated measurement data will be analyzed in a mixed effect model for repeated measurements (ANOVA) with group and time as systematic factors and patients as random effect. The model takes random variations over time into account. Post-hoc tests will be based on the Kenward-Roger approximation to test all included patients despite missing data. The significance level is set at 0.05.

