**Primary objective**

The aim of the study is to evaluate whether tonsillectomy performed with an IDTS is non-inferior compared to tonsillectomy performed with cold steel instruments in terms of PTH and postoperative pain.

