**Outcome Assessment**

Primary endpoints:

- Incidence of PTH defined as hemorrhage requiring hemostasis with bipolar electric coagulation, ligature, compression and/or medical treatment with anti-fibrinolytic within the first 24 hours after surgery (early PTH) until 30 days after surgery (late PTH).
- Intraoperative blood loss assessed by a standardized protocol utilizing the gravimetric method. The nurse suctions up 100 ml of NaCl weighed on the scale for precision (Kern & Sohn, PCB 6000-1). The suction canister is also weighed on the scale, as well as the dry gauze. After the surgery the canister of blood including the NaCl is weighed and the dry weights of the canister and gauze including the NaCl are subtracted, this leaves the total blood loss of the operation. It is assumed that 1 gram blood = 1 ml blood.
- Operative time in minutes from the Boyle-Davis gag is placed until it is removed. The operating nurse is responsible for measurements of time.
- Postoperative pain is assessed on an 11-point numeric rating scale ranging from 0 “no pain” to 10 “worst possible pain”. For children, the Wong-Baker Faces rating scale will be used.

Secondary endpoints:

- Patient reported: Unscheduled contacts to the health care system, patient satisfaction, health related quality of life, and patient reported quality of smell and taste via a validated TASTE questionnaire, followed by further investigation should the patient report altered taste at six months.

Variables:

- Patient reported outcome measures (PROMs) of postoperative recovery (return to normal diet, physical activity, and return to work, school, or childcare), compliance to postoperative recommendations.

**Inclusion criteria:** First time tonsillectomy due to; Tonsillar hypertrophy, recurrent tonsillitis (including previous peritonsillar abscess), chronic tonsillitis, systemic complications to tonsillitis, other (mononucleosis), PFAPA (periodic fever, aphthous stomatitis, pharyngitis, cervical adenitis), tonsillar plugs, peritonsillar abscess and signed written consent.

**Exclusion criteria:** Diseases in the hematopoietic system, antithrombotic or anticoagulant drugs in the recovery period, suspicion of or known malignancy, patients, or parents unable to read or speak Danish, patients, or parents unable to use online application for self-evaluation, patients or parents unable to give informed consent, body weight under 16 kilograms.

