**Power Considerations:** The sample size calculation is based on data from the Danish Tonsil Database. In a twelve months period, the frequency of PTH causing reoperation with hemostasis was 7.9%. With an expected non-inferiority treatment difference between the IDTS and the cold steel instrument, a significance level of 0.05, a power of 80%, and a non-inferiority limit of 4%, the required sample is 1126 patients. Assuming a drop out frequency of 10% into account, a total of 1250 patients are required. With a non-inferiority limit set to 4%, the present study will be able to detect a clinically relevant change in the frequency of PTH causing reoperation with hemostasis.

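### The aim and sample size are for non-inferiority on PTH, but the only test named for categorical endpoints is a test of difference, and no rule links the 4% limit to the analysis

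*Protocol*

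**What the plan says.** Primary objective: the trial is to show whether IDTS tonsillectomy is "non-inferior compared to tonsillectomy performed with cold steel instruments in terms of PTH and postoperative pain". The Discussion repeats non-inferiority as the primary aim.

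Outcome Assessment: the first primary endpoint is "Incidence of PTH defined as hemorrhage requiring hemostasis with bipolar electric coagulation, ligature, compression and/or medical treatment" with an anti-fibrinolytic, up to 30 days. This is a yes/no outcome.

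Power Considerations: in the database, "the frequency of PTH causing reoperation with hemostasis was 7.9" per cent. The calculation is introduced by "With an expected non-inferiority treatment difference between the IDTS and the cold steel instrument", with no figure for that difference. It uses "a significance level of 0.05, a power of 80" per cent and "a non-inferiority limit of 4%, the required sample is 1126 patients", raised to 1250 for 10% drop-out. The paragraph ends: "With a non-inferiority limit set to 4%, the present study will be able to detect a clinically relevant change in the frequency of PTH", again meaning PTH that led to reoperation.

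Statistical analysis: "Endpoints will be evaluated as differences between treatment groups. Categorical data are analyzed by chi2" or Fisher's exact test. A multiple logistic regression handles confounders, a mixed model handles repeated measurements, and the significance level is 0.05. The section mentions no non-inferiority hypothesis, confidence interval or margin. The 4% limit appears only in Power Considerations.

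**The concern.** A non-inferiority trial tests the null hypothesis that the new technique is worse by at least the margin. Chi2 and Fisher's exact test have a different null, that the two rates are equal. Rejecting equality does not answer the non-inferiority question unless the result is also set against the margin. Failing to reject equality may only mean that the data are too few or too noisy.

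The trial is therefore sized for one hypothesis, while the only test named for its main binary endpoint addresses another. PTH is described in the Introduction as potentially life-threatening, and the result is meant to inform whether a gold standard can be replaced. The rule for declaring success should not be left to be inferred after the data are seen.

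**Working it through.** **Inputs.** From Power Considerations: control rate 7.9%, limit 4%, level 0.05 (sidedness not stated), power 80%, 1126 patients. From Design: equal allocation. Assumptions, because the protocol gives no figure: true difference zero, and a limit in absolute percentage points.

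**Step 1. Reproduce 1126.** For non-inferiority of two proportions with equal true rates p and margin d:

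n per arm = (z for level + z for power)² × 2p(1−p) / d²

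One-sided 0.05: (1.645 + 0.842)² × 2 × 0.079 × 0.921 / 0.04² = 6.183 × 0.1455 / 0.0016 = 562.3, so 563 per arm and **1126 in total, an exact match**. Allowing for 10% drop-out, 1126 / 0.9 = 1251, or 1252 in two equal arms, against the stated 1250 (rounding).

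Alternatives do not match. One-sided 0.025 gives 714 per arm, 1428 in total. A two-sided 0.05 difference test of 7.9% against 11.9% gives 1748. The stated figure is thus a non-inferiority sample size at one-sided 0.05.

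**Step 2. One data set, two answers.** Take 44/563 (7.8%) on cold steel and 60/563 (10.7%) on IDTS.

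- Difference: 16/563 = 2.84 points.
- Standard error: √[(0.0782 × 0.9218 + 0.1066 × 0.8934) / 563] = 1.72 points.
- Chi2 p = 0.10; Fisher p = 0.12. No significant difference.
- Upper limit, 90% interval: 2.84 + 1.645 × 1.72 = 5.7 points. Upper limit, 95% interval: 6.2 points.

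Both upper limits exceed 4, so non-inferiority is not shown. With 44 control events, every IDTS count from 52 to 63 behaves this way: chi2 is non-significant, yet the 90% upper limit is above 4 points.

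**Step 3. How often the two would diverge.** Exact enumeration of two binomial arms; uncorrected chi2 at two-sided 0.05; margin rule = upper limit of the Wald 90% interval below 4 points.

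| True rates (cold steel, IDTS) | Per arm | Chi2 non-significant | Margin rule met |
|---|---|---|---|
| 7.9%, 11.9% | 563 | 38.2% | 5.2% |
| 7.9%, 11.9% | 625 | 33.8% | – |
| 7.9%, 7.9% | 563 | 95.0% | 80.2% |

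Hand check of the first row by normal approximation: the pooled standard error is √(2 × 0.099 × 0.901 / 563) = 1.780 points and the unpooled one is 1.776. Then Φ[(1.96 × 1.780 − 4) / 1.776] = Φ(−0.29) = 0.39, in line with 38.2%.

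With equal true rates, 17.3% of trials at 563 per arm are non-significant by chi2 and still fail the margin.

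**Step 4. Power of a margin rule at 1126.** With equal rates, the standard error is √(0.1455 / 563) = 1.608 points, and 4 / 1.608 = 2.488.

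- One-sided 0.05 (90% interval): Φ(2.488 − 1.645) = 0.80; exact 80.2%.
- One-sided 0.025 (95% interval): Φ(2.488 − 1.960) = 0.70; exact 70.1%. Reaching 80% at this level needs 1428 evaluable patients, 1587 with 10% drop-out.

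**The case against.** **The section is generic.** It names no endpoint, its opening sentence could mean estimating a risk difference, the margin is already fixed in Power Considerations, and interval details are often left to a statistical analysis plan, which is not at hand here. This stands in part: the choice of interval method is not a defect of the protocol. But the protocol does not leave the test open. It assigns chi2 or Fisher to categorical data, PTH is categorical, and nothing says how the limit enters the conclusion. A later plan with a margin rule would have to add to this section or depart from it.

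**Stronger readings that the document does not support.**

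- A reader might infer that the investigators will treat p > 0.05 as proof of non-inferiority. No passage says so. The 38% and 34% figures are conditional on that reading and show why a rule is needed; they are not the error rate of the plan as written.
- A reader might infer from the word detect in Power Considerations that the trial is underpowered, since a two-sided difference test of 7.9% against 11.9% has only about 61% power at 1126. The trial was not sized for that test, and 1126 is reproduced exactly as a non-inferiority figure. The wording is loose, but the number is not wrong.
- A reader might fault the logistic regression because odds ratios do not map directly onto an absolute margin. The protocol gives that model a confounder role, not the primary non-inferiority test.
- Pain is also in the non-inferiority objective and has no margin. That is a separate point with a separate remedy and adds nothing to the case on PTH.

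**Conclusion.** The mismatch is real and internal to the protocol. The objective and sample size are for non-inferiority on PTH, the named test for categorical data is for difference, and no decision rule connects the 4% limit to the analysis. Chi2 or Fisher alone cannot establish non-inferiority. This should be corrected before PTH is compared by arm.

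On size: if, and only if, non-significance were taken as non-inferiority, about 38% of trials at 563 per arm (34% at 625) would make a false claim at a true 4-point excess, against about 5% for a margin test at one-sided 0.05.

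These figures assume a 7.9% control rate, an absolute margin, equal arms and a Wald interval. The 7.9% is the rate of PTH causing reoperation, whereas the endpoint counts a wider set of treatments, so the rate in the trial may differ. One-sided 0.05 is inferred because it reproduces 1126; the protocol never states it.

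**What to change.** In Statistical analysis:

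1. Make the primary PTH analysis the risk difference, IDTS minus cold steel, with a confidence interval. Conclude non-inferiority only if the upper limit is below 4 percentage points.
2. State the level. One-sided 0.05 (two-sided 90% interval) is the one that reproduces 1126, with about 80% power. If one-sided 0.025 (two-sided 95% interval) is chosen, restate the power as about 70% at 1126 evaluable patients.
3. Keep chi2 or Fisher for a superiority comparison or for other endpoints.

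In Power Considerations, state the sidedness, the assumed true difference and that the limit is absolute. Replace the closing sentence on detecting a change with a statement that the trial is designed to rule out a PTH excess of 4 points or more.

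Cost: a change of wording, with no new data. No extra patients are needed at the level that reproduces 1126. Keeping 80% power with a 95% interval would require 1428 evaluable patients (1587 with drop-out), so the choice should be made openly and before any comparison by arm.

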**Method**

*Design*

The project is designed as a Danish randomized controlled multi-center trial of tonsillectomy by conventional cold steel surgical technique versus IDTS. The study is blinded for patients until six months after surgery and the study is assessor blinded.

Randomization is computerized via the tonsil database and utilizes block randomization for each department in a random table of 2000 with equal numbers of group assignments. The randomization is only apparent to the surgeon on the day of the surgery and the day before.

*Course*

All elective and acute patients referred to tonsillectomy, with or without adenoidectomy, on benign indications will be assessed for eligibility at the participating ENT departments. Given a signed declaration of consent patients will be enrolled and randomized in the study to either the standard cold steel tonsillectomy or to IDTS tonsillectomy.

After surgery all patients will be brought to the recovery room for 1-4 hours or hospitalized for a day. Before hospital discharge a surgeon will check for postoperative hemorrhaging and the patient and caregivers will receive oral and written recommendations for the postoperative period. Patients or caregivers are requested to follow the recommendations, and they are instructed to contact the ENT department or to call an ambulance, if postoperative hemorrhage occurs.

There will be no planned postoperative visits at the hospital. During the first six postoperative months included patients/caregivers are asked to complete electronic questionnaires online on their mobile device: daily, for the first two postoperative weeks, and again one month and six months postoperatively.

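### The test named for post-tonsillectomy hemorrhage is a test of equality that does not use the 4% limit, although the trial is posed and sized as non-inferiority

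*Protocol*

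**What the plan says.** - **Primary objective:** the stated aim reads "evaluate whether tonsillectomy performed with an IDTS is non-inferior compared to tonsillectomy performed with cold steel instruments in terms of PTH and postoperative pain". The Discussion repeats the non-inferiority question for PTH.
- **Outcome Assessment:** the incidence of PTH up to 30 days is a primary endpoint. It counts bleeding treated by coagulation, ligature, compression or anti-fibrinolytic drugs.
- **Power Considerations:** in the Danish Tonsil Database "the frequency of PTH causing reoperation with hemostasis was 7.9" percent. The calculation takes "a power of 80%, and a non-inferiority limit of 4%, the required sample is 1126 patients", at a significance level of 0.05 whose sidedness is not given.
- **Statistical analysis:** endpoints are judged on the difference between groups, and "Categorical data are analyzed by chi2 or Fisher’s exact test". A multiple logistic regression handles confounders, and the level is again 0.05. The section does not mention non-inferiority, the 4% limit or a confidence interval for PTH. The limit appears only under Power Considerations.

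**The concern.** PTH is categorical, so the sentence on chi2 and Fisher's exact test governs it. The null hypothesis of both tests is that the two rates are equal, whereas the null hypothesis of a non-inferiority test is that IDTS is worse by at least 4 points. A non-significant equality test does not reject that second null: it can arise with an upper confidence limit well above 4 points. The logistic regression does not fill the gap, because no margin is attached to it and it works on the odds-ratio scale.

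At stake is whether the main claim of the trial has a prespecified basis. Followed as written, the plan yields a p-value that usually leaves the non-inferiority question open. The power quoted to justify the sample size is that of a different test.

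**Working it through.** **Inputs.** Control rate 7.9%, limit 4%, level 0.05, power 80% (Power Considerations). Allocation 1:1, from "a random table of 2000 with equal numbers of group assignments" (Method, Design). The protocol gives no figure for the expected difference; 0 is assumed because it reproduces the sample size. The limit is taken as an absolute difference for the same reason.

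**1. Reproduce the sample size.** For a margin test at one-sided 0.05:

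n per arm = (1.645 + 0.842)² × 2 × 0.079 × 0.921 / 0.04² = 562.3, so 563 per arm and 1126 in total. This matches the protocol exactly.

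Other readings do not match:
- margin test at one-sided 0.025: 714 per arm, 1428 in total;
- equality test of 7.9% against 11.9%: 1378 (one-sided) or 1748 (two-sided);
- equality test of 7.9% against 3.9%: 858 (one-sided) or 1088 (two-sided).

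The design therefore used a margin test at one-sided 0.05.

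**2. Compare the two tests.** The table enumerates all binomial outcomes at 563 per arm with a 7.9% control rate. Chi2 is two-sided at 0.05. The margin test passes if d + 1.645 × SE < 0.04, where d is the observed difference (IDTS minus cold steel) and SE its unpooled standard error.

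| True excess on IDTS | Chi2 non-significant | Margin test passes | Chi2 non-significant, non-inferiority not shown |
|---|---|---|---|
| 0 | 95.0% | 80.2% | 17.3% |
| +2 points | 78.2% | 32.6% | 45.7% |
| +4 points (at the limit) | 38.2% | 5.2% | 33.0% |

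Hand check at +4 points: the pooled SE is √(2 × 0.099 × 0.901 / 563) = 0.01780 and the unpooled SE is √((0.079 × 0.921 + 0.119 × 0.881) / 563) = 0.01776. The chance of non-significance is Φ((1.96 × 0.01780 − 0.04) / 0.01776) ≈ 38.7%, close to the exact 38.2%. With 625 per arm (1250 and no dropout) the exact figures at +4 points are 33.8% and 5.2%.

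**3. When the named test does settle the question.** A significant result favouring IDTS implies non-inferiority. Under equal rates this occurs in about 2.5% of trials, half of the two-sided 5%.

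**4. One possible result.** 44/563 (7.8%) on cold steel and 61/563 (10.8%) on IDTS give a difference of 3.02 points. The pooled SE is 1.733 points, so z = 1.74; chi2 p = 0.081 and Fisher p = 0.101. The upper one-sided 95% limit is 3.02 + 1.645 × 1.731 = 5.9 points. The named test finds no significant difference, yet an excess above 4 points is not excluded.

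**5. Sensitivity to the control rate.** The 7.9% is a rate of reoperation, and PTH as defined under Outcome Assessment may have a different rate. With the formula of step 2 and assumed control rates either side, a 4-point excess leaves chi2 non-significant in:
- 6% against 10%: Φ((1.96 × 0.01617 − 0.04) / 0.01613) ≈ 30%;
- 10% against 14%: Φ((1.96 × 0.01937 − 0.04) / 0.01933) ≈ 46%.

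The margin test passes in about 5% in both cases.

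**6. Level of the interval.** With equal rates of 7.9% and 1126 evaluable patients, the one-sided 95% limit gives 80.2% power and the upper end of a two-sided 95% interval gives 70.2%. With the latter, 80% power needs 1428 evaluable patients, or 1428 / 0.9 = 1587 with 10% dropout.

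**The case against.** **An analysis plan may add the margin test.** It may exist, and detail of this kind is often left to it. But the protocol does not leave the test open: it names one that does not match its hypothesis. A later plan with a margin test would depart from the protocol's rule, so the rule needs correcting either way.

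**Judging endpoints on group differences leaves room for a risk difference.** It does, but no interval or comparison with 4% is attached, and the next sentence names equality tests.

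**An equality test can show non-inferiority.** This stands. A reader might infer that the named test can never answer the question; that is too strong, because superiority of IDTS implies non-inferiority. The case is not remote: the Introduction cites a 4.5% PTH rate for the device. At 4.5% against 7.9%, chi2 would favour IDTS in Φ((0.034 − 1.96 × 0.01437) / 0.01434) ≈ 66% of trials. That helps only if IDTS is truly much better. The sample size rests on equal rates, where the figure is 2.5%.

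**The 38% is hypothetical.** This also stands. A reader might infer that the protocol will declare non-inferiority whenever p exceeds 0.05. No sentence says so. The figure measures a misreading that the text leaves open, not a stated rule.

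**Conclusion.** The mismatch is real and concerns a primary endpoint. The question and the sample size are those of a 4-point margin test, and the named analysis is a test of equality. The quoted 80% power does not describe that analysis.

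The size depends on 563 per arm, a 7.9% control rate that comes from reoperations, and a limit read as an absolute difference. On that basis, even truly equal rates leave about 17% of trials with a non-significant chi2 and non-inferiority not shown. At a true 4-point excess, chi2 is non-significant in about 38% of trials (roughly 30% to 46% for assumed control rates of 6% to 10%), against about 5% passing a margin test. The 38% is a false-claim rate only if non-significance is taken as proof.

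The documents do not support saying that the trial is unable to show non-inferiority. The same two-by-two table yields the interval that is needed. The rule should be corrected before the treatment comparison is seen, because it decides whether the main claim can be made.

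**What to change.** In Statistical analysis, add a rule for PTH:

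- Estimate the risk difference, IDTS minus cold steel, with a confidence interval.
- Declare IDTS non-inferior only if the upper limit is below 4 percentage points.
- State the level. A one-sided 95% limit, which is the upper end of the two-sided 90% interval, matches the sample size and gives 80% power. If a two-sided 95% interval is preferred, restate the power at 1126 as about 70%, or plan for 1428 evaluable patients.
- For PTH, use chi2 or Fisher's exact test only as a superiority step after non-inferiority has been shown. Keep these tests for other categorical variables.
- State that a non-significant equality test is not evidence of non-inferiority.

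**Cost:** a few sentences. No further data are needed, and no further patients if the one-sided 95% limit is adopted. The downside is a success criterion stricter than the absence of a significant difference. The rule covers PTH alone; it does not deal with the other primary endpoints or the interim analysis.

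### A normality check on the trial data picks the test for operative time and blood loss, and neither an effect estimate nor a department term is fixed

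*Protocol*

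**What the plan says.** Outcome Assessment lists four primary endpoints. Two are continuous and measured once per patient:

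- "Intraoperative blood loss assessed by a standardized protocol utilizing the gravimetric method"
- "Operative time in minutes from the Boyle-Davis gag is placed until it is removed"

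The Statistical analysis section opens with "Endpoints will be evaluated as differences between treatment groups". For continuous outcomes it then says "Depending on normal distribution, continuous data is analyzed by either un-paired Student", with the Mann-Whitney rank sum test as the other option. It does not say how normality is to be judged.

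Three other statements bear on the point:

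- "Stratification will be performed", with no factor and no endpoint named.
- "confounding factors (sex, age, surgical indication, BMI, smoking, comorbidity) analyzed in a multiple logistic regression model". This is a model for binary outcomes, and its list contains neither department nor adenoidectomy.
- A mixed model, which is for repeated measurements and so does not cover these two endpoints.

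Under Method, the Design paragraph says that randomisation "utilizes block randomization for each department". The Course paragraph says who is assessed for eligibility: "All elective and acute patients referred to tonsillectomy, with or without adenoidectomy".

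**The concern.** The t-test and the Mann-Whitney test answer different questions. One compares means; the other compares the ordering of values. If a check on the outcome data decides between them, the quantity being compared is not known until the data are in, and it could differ between the two endpoints. The section promises differences but does not say which difference (mean, location shift or ratio) will be reported, or with what interval. The closing paragraph of the Discussion counts surgery time among the outcomes on which non-inferiority is tested, and that needs an estimate with a confidence limit.

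The second part is precision. Allocation is blocked within department, and the Discussion itself warns of differences in practice between centres. The stated two-group tests nevertheless carry no department term. Patients having adenoidectomy are enrolled alongside those who are not. If the adenoidectomy falls within the gag interval, which the definition does not settle, it adds variation to operative time that a model could remove.

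**Working it through.** **Size of the comparison.** The Protocol gives no sample size for these two endpoints. Its figure for haemorrhage reproduces with p = 0.079 in both arms, margin 0.04, one-sided 0.05 and 80% power:

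n per arm = (1.645 + 0.842)² × 2 × 0.079 × 0.921 / 0.04² ≈ 563, so 1126 in total.

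The checks below use about 563 per arm.

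**Shape of operative time.** The Introduction gives pilot values of median 5.1 and range 1.5 to 26.5 minutes; the reference list gives 186 patients.

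- Above the median: 26.5 − 5.1 = 21.4 minutes. Below it: 5.1 − 1.5 = 3.6 minutes. Ratio 21.4 / 3.6 = 5.9, which is right skew.
- Assuming a lognormal shape, with the extremes of 186 values about 2.71 SD from the centre, log-SD = ln(26.5/1.5) / (2 × 2.71) = 0.53.

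For blood loss the Introduction gives only 1 to 10 ml, which does not fix a shape.

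**Where a formal check would lead.** Shapiro-Wilk test at 0.05, 400 simulated lognormal samples of 563 for each value:

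| Log-SD | Skewness | Normality rejected |
|---|---|---|
| 0.1 | 0.30 | 72% |
| 0.2 | 0.61 | 100% |
| 0.3 | 0.95 | 100% |
| 0.53 | 1.89 | 100% |

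**Type I error.** 3000 simulated null trials, 563 per arm, log-SD 0.53: 0.051 for the t-test and 0.053 for Mann-Whitney.

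**Precision.** 500 simulated trials per row, each with five departments of 226 patients, a baseline median of 7 minutes, log-SD 0.53 and a true difference of −0.6 minutes. The department spread and the adenoidectomy share and added time are assumptions, as are the baseline and the difference. The standard errors are for the mean difference in minutes from a linear model, without and with department and adenoidectomy. Half-width = 1.96 × SE.

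| Department log-SD | Adenoidectomy | SE unadjusted | SE adjusted | Ratio | 95% half-widths (min) |
|---|---|---|---|---|---|
| 0.1 | +1 min in 30% | 0.281 | 0.277 | 1.02 | 0.55 vs 0.54 |
| 0.3 | +3 min in 30% | 0.333 | 0.294 | 1.13 | 0.65 vs 0.58 |
| 0.3 | +5 min in 50% | 0.361 | 0.298 | 1.21 | 0.71 vs 0.58 |

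A direct calculation for adenoidectomy alone gives a similar upper size. Assume 40% of patients have it, adding 8 minutes, with a tonsillectomy-time SD of 5 minutes and 625 per arm:

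- Total SD = √(25 + 0.4 × 0.6 × 64) = 6.35.
- Half-widths: 1.96 × 6.35 × √(2/625) = 0.70 against 1.96 × 5 × √(2/625) = 0.55 minutes, a gap of about 9 seconds.

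With 20%, 5 minutes and SD 8, the half-widths are 0.91 and 0.89 minutes.

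**Which difference.** In one simulated data set with medians of 7 and 5.1 minutes, the Hodges-Lehmann shift was −1.9 minutes and the mean difference −2.4. The two are not interchangeable, so the choice needs stating.

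**The case against.** The strongest reply has five parts.

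1. **A rank test need not lack an estimate.** A Hodges-Lehmann shift with interval, in minutes or ml, can accompany Mann-Whitney, and the choice of estimate is commonly left to a statistical analysis plan, which is not shown here. This stands against the inference that no difference can be reported. It does not answer the data-driven choice of test, which the Protocol itself fixes.
2. **Stratification is mentioned.** A rank test can be stratified by department, and the section says stratification will be done. A reader might infer that department is certainly ignored. The text does not support that; it supports only that no factor is named for these endpoints.
3. **No formal normality test is named.** A reader might infer that Mann-Whitney is certain. Plots or a transformation would also fit the wording, and simulating lognormal data partly presupposes the answer. The pilot range is from the sealer only and rests on two extreme values. Very likely for operative time under a formal test is as far as it goes; for blood loss nothing follows.
4. **The adenoidectomy inputs have no source in the Protocol.** True; they are assumptions and only show a range.
5. **The rank test is not weak here.** In the three simulated settings its power, with no stratification, was 81%, 68% and 52%, against 59%, 56% and 54% for the adjusted linear model and 57%, 47% and 41% for the unadjusted one. With strong skew it did better than the adjusted model in two of three. So the SE ratios describe adjusted against unadjusted differences in minutes; they do not show that Mann-Whitney wastes power. This stands, and it is a reason to keep a rank test and a log-scale analysis in support.

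**Conclusion.** The point holds as an improvement to the analysis, at low severity. For two listed primary endpoints the Protocol lets the data choose between two tests that target different quantities. It ties neither to an estimate or interval, and it names no department term although allocation is blocked by department. The covariates it lists belong to a logistic model, which does not serve minutes or ml.

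A reader might infer that the results would be biased or the error rate inflated. They would not: randomisation protects the comparison from systematic imbalance in department or adenoidectomy, and both tests held their level in simulation. That simulation had no department effects, but ignoring a blocking factor tends to make an unadjusted test conservative.

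The cost is a less interpretable result and a modest loss of precision in the difference in minutes. The SE ratio is 1.02 to 1.21, which is 0.01 to 0.12 minutes of confidence-interval half-width in the simulated settings. These sizes rest on the assumed department and adenoidectomy effects and the lognormal shape taken from the pilot range.

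**What to change.** Remove the normality-based choice for operative time and blood loss. For each, prespecify one linear model with treatment group and department, using robust standard errors. For operative time, add concurrent adenoidectomy (yes/no) if the register records it. The Introduction says the database holds per-operative information, but adenoidectomy is not mentioned there, so this should be confirmed.

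Report the adjusted difference in minutes or ml with its 95% CI. Add a log-scale analysis giving a ratio as a sensitivity analysis, and a department-stratified rank test as supportive. State which factor the stratification sentence refers to and which endpoints it covers.

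The cost is analysis wording only. Sample size, randomisation and conduct do not change.
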